### Sub-studies

As of today, many data exist regarding possible risks and complications when using conventional thermal energies for AF ablation. In contrast, few data and no randomized assessments are available regarding the use of PFA. In particular, studies investigating PFA and oesophageal safety, PFA and the risk of cerebral lesions, its impact on vagal response, and the autonomic nervous system (ANS) are very limited. Additionally, we aimed to assess the need for redo procedures related to PV reconnection and recurrent arrhythmia mechanisms as well as the impact of PFA on atrial and ventricular function. Five sub-studies were thus designed for these objectives. Participants in the main study were offered optional participation in sub-studies. Informed consent is given separately for each sub-study and separately from the main study. Participants are free to take part in the main study without participating in any of the sub-studies, and they are free to participate in as many sub-studies as they wish, among those offered in their site.

### Oesophageal safety

We hypothesize that PFA is associated with fewer or no oesophageal lesions, as compared with RF. Participants were offered systematic oesophagoscopy 1–3 days after index ablation in both arms. As atrio-oesophageal fistulas are rare, oesophageal lesions related to AF ablation will be used as a surrogate, and we will compare their incidence and characteristics, between PFA and RF.^13^ The video recordings will be centrally analysed and categorized by a core lab blinded to the study procedure. In patients enrolled into ‘Atrial and ventricular imaging’ sub-study (see below), acute MRI will also be used to assess acute oesophageal injury after ablation.

### Brain magnetic resonance imaging

In this sub-study, we postulate that PFA—being a non-thermal catheter ablation modality—is not associated with an increased risk for cerebral lesions as opposed to RFA and there are no differences in the evolution of lesions. The sub-study objectives will be to compare groups on the occurrence of acute ischaemic or haemorrhagic cerebral lesions and their 2-month evolution, as assessed with brain MRI. Participants with symptomatic cerebral events (stroke/TIA) will be subjected to acute brain MRI dictated by clinical reasoning. All sub-study participating patients underwent a brain MRI (diffusion-weighted imaging, fluid attenuated inversion recovery, susceptibility-weighted imaging) on Days 1–3 following the index ablation procedure. In addition, those patients with positive baseline MRI (demonstrating acute ischaemic or haemorrhagic lesions) will have a follow-up MRI after 2 months. All MRIs will be analysed centrally and blinded to the study procedure.

### Autonomic nervous system

We expect that PFA has a less significant impact on cardiac ANS function compared with thermal energy sources. For this investigation, we aim to describe the acute and 1-year change in cardiac ANS outcomes. Participants in this sub-study underwent a limited intraprocedural EP study, including extracardiac right vagal nerve stimulation to evaluate the extent of vagal denervation (immediately after left and right PV ablation). In addition, they will undergo serial atropine testing and heart rate variability assessment up to 12 months of follow-up.

### Redo procedures

The frequency of redo procedures is expected to be less in the PFA group, mostly because of more durable lesions and thus fewer PV reconnections. We aim to evaluate the prevalence of electrical PV reconnection after PFA as compared with standard RF. We also want to understand if recurrent atrial arrhythmias are associated with PV reconnections and to determine if the recurrent arrhythmia mechanisms are different after PFA vs. RF index ablation. Therefore, high-density CARTO maps from redo procedures (as clinically indicated) will be analysed in detail.

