## Introduction

Performing catheter ablation has emerged as a well-excepted therapeutic approach for the treatment of patients with symptomatic paroxysmal atrial fibrillation (AF).^1–3^ Thermal-based energy sources [radiofrequency (RF) energy/cryo energy] for catheter ablation are considered effective and reasonably safe in this indication.^2,4^ However, treatment success remains limited with single-procedure success rates between 60% and 80%.^5–8^ Pulmonary vein reconnection is believed to be a main underlying factor limiting treatment success. Therefore, creating more durable lesions when performing catheter ablation has been a major focus of scientific investigation within the field of clinical electrophysiology over the last decade.^9,10^ Furthermore, thermal ablation strategies can result in rare yet significant complications since these methods ablate all types of tissue in a non-selective manner.^11–13^ Pulsed field ablation (PFA) is a novel, non-thermal ablation strategy based on pulsed electric field (PEF) energy delivery. This energy source allows highly selective cardiac ablation that resulted in safe, durable, and transmural lesions as demonstrated in smaller studies.^14,15^ The BEAT PAROX-AF trial aims to provide comparative evidence of PEF vs. RF ablation in terms of efficacy and safety when treating patients with paroxysmal AF. The primary objective of the trial is to test the superiority of PFA over standard RF catheter ablation on the rate of 1-year recurrence of atrial arrhythmia. We hypothesize that PEF energy, a non-thermal ablative modality highly specific for cardiac cells, will deliver more durable PVI than RF energy, translating into superior clinical outcomes for PFA as compared with RF energy. By evaluating the outcomes of PFA, the study aims to provide critical insights into the optimal treatment approach for paroxysmal AF, to improve their clinical outcomes, including quality of life, and procedural duration.

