### Sample size

Radiofrequency has been reported to provide around 65% single-procedure success rate in paroxysmal AF.^23,24^ A success rate of 80% could be expected with PEF.^25^ With a type I error rate of 5%, a power of 80%, and randomization with a 1:1 ratio, we need to include 276 participants (138 participants in each arm). After accounting for a maximum of 5% of missing data at 12 months, the total sample size was increased to 292 participants (146 participants in each arm).

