### Statistical methods

Primary analyses will be conducted according to the intention-to-treat principle, in which all randomized patients will be included in the arm in which they first were randomized, and all their data will be used. The comparisons of the single-procedure 1-year success rates between the PEF arm and the RF arm will use logistic mixed models with a random effect on the study centres and fixed effects on the procedure arms, with a two-sided type I error rate of 5%. The model will be adjusted on major prognostic factors (common ostia, intermediate PV, PV diameter > 25 mm, and body mass index). For secondary objectives, linear (for quantitative outcomes) and logistic (for binary outcomes) mixed models will be used to compare the outcomes between the arms. The assumption of the models will be systematically checked.

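### Reconnection found at clinically indicated redo procedures does not estimate the prevalence of PV reconnection after each treatment; the comparison needs all randomised patients in the denominator

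*Protocol article*

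**What the plan says.** The Redo procedures paragraph under Sub-studies (Protocol article) sets a between-arm aim: "We aim to evaluate the prevalence of electrical PV reconnection after PFA as compared with standard RF". It then fixes the source of the data: "high-density CARTO maps from redo procedures (as clinically indicated) will be analysed in detail". The Abstract likewise says that durability of isolation is assessed at redo procedures. Table 1 schedules the CARTO export only at the index procedure and at redo, and no remapping of patients without a redo is described.

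Four other statements bear on who is mapped:
- The Redo procedures paragraph expects fewer redos after PFA, mainly through more durable lesions and fewer reconnections.
- Primary endpoint: a redo for atrial arrhythmia other than typical flutter counts as failure.
- Blinding: patients and clinical staff know the allocation.
- Sub-studies: participation is optional.

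Durability also carries the trial's rationale. The Introduction hypothesises that pulsed field energy "will deliver more durable PVI than RF energy, translating into superior clinical outcomes for PFA".

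**The concern.** The stated target is how often veins reconnect after each treatment. The patients who can show it are those who came to a redo. Entry to that group happens after randomisation, is decided by staff who know the arm, and is expected to differ by arm through the quantity being measured. Randomisation does not protect a comparison made inside such a group.

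Readers are likely to take the reconnection rates at redo as evidence on the durability hypothesis in the Introduction. As planned, the two percentages would describe redo patients and not the treatments, and the contrast between them can be trusted only under an assumption about redo decisions that the open-label design does not secure.

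**Working it through.** **The plan's own figures.** The only numerical design figure is the primary sample size. Inputs (Sample size section): "Radiofrequency has been reported to provide around 65% single-procedure success rate in paroxysmal AF" and "A success rate of 80% could be expected with PEF"; power 80%, 1:1 allocation, and a 5% type I error that the Statistical methods section makes two-sided. With pooled variance and no continuity correction:

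n = [1.960·√(2·0.725·0.275) + 0.842·√(0.65·0.35 + 0.80·0.20)]² / 0.15² = 137.9, so 138 per arm. Then 138/0.95 = 145.3, so 146 per arm and 292 in all.

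Both figures reproduce. They do not bear on the redo comparison, for which no size is given, but they show how many patients could be mapped:
- Planned failures: 146 × 0.35 = 51 RF and 146 × 0.20 = 29 PFA. If every failure and no one else had a redo, about 80 of 292 would be mapped (27%).
- If half of failures had a redo (an assumption; the article gives no redo rate): about 26 RF and 15 PFA.

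**Formula.** Let q be the probability of reconnection among all randomised patients in an arm, and r1 and r0 the probabilities of reaching a redo with and without reconnection. Then

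P(reconnected | redo) = q·r1 / [q·r1 + (1−q)·r0],

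and the odds of reconnection at redo are [q/(1−q)] × [r1/r0]. All values of q, r1 and r0 below are assumptions.

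**Same selection in both arms** (redo taken to follow recurrence; a common share of recurrences redone cancels out).

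| r1 / r0 | True RF vs PFA | At redo RF vs PFA | Risk ratio, true → redo | Gap in points, true → redo | Odds ratio, true → redo |
|---|---|---|---|---|---|
| 0.60 / 0.15 | 40% vs 20% | 0.24/0.33 = 73% vs 0.12/0.24 = 50% | 0.50 → 0.69 | 20 → 23 | 0.375 → 0.375 |
| 0.70 / 0.10 | 40% vs 20% | 0.28/0.34 = 82% vs 0.14/0.22 = 64% | 0.50 → 0.77 | 20 → 19 | 0.375 → 0.375 |
| 0.60 / 0.10 | 50% vs 20% | 0.30/0.35 = 86% vs 0.12/0.20 = 60% | 0.40 → 0.70 | 30 → 26 | 0.25 → 0.25 |

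The last row matches the plan's failure rates of 35% and 20%. In every row both levels are inflated and the risk ratio moves toward 1. The odds ratio does not change, because r1/r0 cancels between arms. For the same reason, equal reconnection at redo would mean equal true reconnection.

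**Selection that differs by arm, no true difference.** One arm has r1/r0 = 0.5/0.1.

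| q in both arms | First arm at redo | Other arm, 0.5/0.2 | Other arm, 0.4/0.2 |
|---|---|---|---|
| 30% | 0.15/0.22 = 68% | 0.15/0.29 = 52% (gap 16) | 0.12/0.26 = 46% (gap 22) |
| 50% | 0.25/0.30 = 83% | 0.25/0.35 = 71% (gap 12) | 0.20/0.30 = 67% (gap 17) |

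The spurious odds ratio is (0.5/0.1)/(0.5/0.2) = 2.0 or (0.5/0.1)/(0.4/0.2) = 2.5.

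**Selection that differs by arm, true difference hidden.** Take true reconnection of 40% RF and 20% PFA, with r1/r0 = 0.4/0.2 in RF and 0.5/0.1 in PFA. At redo, RF shows 0.16/0.28 = 57% and PFA shows 0.10/0.18 = 56%.

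**All-randomised endpoint.** A redo showing reconnection has probability q·r1.
- Equal selection, first row of the first table: 0.12/0.24 = 0.50, the true ratio.
- Null scenarios: 0.15 vs 0.15 or 0.12, and 0.25 vs 0.25 or 0.20, so gaps of 0 to 5 points instead of 12 to 22.
- Hidden-difference example: 0.10/0.16 = 0.63 against a true 0.50. The endpoint is free of r0 but not of differences in r1.

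**The case against.** The strongest case against is that conditioning on redo need not bias the comparison. If redo depends on reconnection status in the same way in both arms, the odds ratio and the null are preserved. The only binary-outcome method that the article names is the logistic mixed model, although Statistical methods does not expressly extend it to the sub-studies. This point stands. A reader might infer that redo-only rates must pull the arms together, or that similar rates would necessarily conceal better durability. The documents do not support that: under equal selection the absolute gap can widen (20 to 23 points above), and a hidden or false difference needs arm-specific selection.

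It does not rescue the aim as written. The target is prevalence, which is inflated in both arms even under equal selection, and open-label redo decisions give no assurance that selection is equal.

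A reader might also infer that the trial draws a mechanistic conclusion from this subset. It does not: the sub-study states an aim, with no test or durability conclusion, and the Abstract is open that durability is assessed at redo.

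It can further be said that redo already enters two all-randomised outcomes (primary failure, and repeat ablations under healthcare use), and that denominators may be left to a fuller document. Neither outcome counts reconnection, however, and the article itself fixes both the target and a data source that cannot deliver it.

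Finally, the proposed endpoint shares part of the weakness. That is true and has to be declared.

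**Conclusion.** The point holds in limited form. Reconnection among redo patients does not estimate reconnection after PFA or after RF. Both levels are too high whenever reconnected patients are likelier to reach a redo, which the article's own expectation implies, and the risk ratio is distorted (0.50 to 0.69 or 0.77, or 0.40 to 0.70, in the assumed examples). The odds ratio and the null survive only if selection into redo, given reconnection status, is the same in both arms. If it is not, a gap of 12 to 22 points can appear from nothing, or a true 20-point gap can shrink to about 2, under the assumed probabilities.

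The redo rate and the selection probabilities are assumptions throughout, so the documents fix neither the direction nor the size of any bias. The matter is confined to the sub-study; the randomised primary comparison is unaffected. The change is worth making because it is nearly free and settles what the sub-study can conclude.

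**What to change.** In the redo sub-study, define the between-arm comparison as a redo by 12 months that shows at least one reconnected pulmonary vein. Use all randomised patients in the denominator and count patients without a redo as having no event. Report reconnection and arrhythmia mechanism among redo patients as descriptive and conditional on redo, and do not label them prevalence or durability by arm.

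The cost is analysis wording. The Redo procedure section under Interventions already has reconnections documented at every redo, so no new data are needed; because sub-study participation is optional, the endpoint should draw on that main-study record.

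Two limits should be stated with the result: the endpoint still depends on an unblinded decision to redo, and it counts silent reconnection as no event.

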### Atrial and ventricular imaging

We expect unchanged atrial morphology (including PV diameter) and function when PVI is performed with non-thermal PFA energy. This sub-study will compare the impact of PFA vs. RF on LA function, left ventricular (LV) structure and function, and acute and chronic tissue changes after ablation. Participants will be offered high-resolution cardiac MRI (cine and late gadolinium enhancement) at baseline and 2 months, and a sub-set of participants will be offered an additional acute cardiac MRI just after the index ablation. Cine images will be processed to assess atrial strain, reservoir, and contractile LA function as well as LV ejection fraction.

### Data management

Different tasks of data management (from study design to database closure) and the responsibilities of each person involved in the data management process and quality control are detailed in a data management plan. Clinical data are collected by using an eCRF (screening, baseline, and follow-up data). Any original document or information recorded during the study is defined as a source document, and the eCRF must accurately reflect the data in the source document. Source documents in the framework of the study can be paper CRF, original copies of scales, or medical files. Consistency checks will be programmed by the data manager to check the consistency and the completion of data in the eCRF. The list of consistency checks will be predefined by the project team and passed on to the data manager who will write a study-specific data validation plan. Additional queries might also be raised by the clinical research assistant. Queries are sent to the clinical site via the eCRF. Remote and on-site monitoring is organized throughout the trial to ensure compliance with the protocol, regulations, and good clinical practice recommendations. Complex data comprising images (MRI, CT, TTE, X-rays, endoscopy) and signals (ECG, Holter, electroanatomic mapping) will be pseudonymized by each clinical partner using participant ID and stored in the Electrophysiology and Heart Modelling Institute (Lyric) of the University of Bordeaux (UBx) (UBx-Liryc) database.

### Auditing

Audits of the trial will be periodically arranged by reviewing the data obtained as well as the procedural aspects of the trial. This may include on-site audits and source data checks. Direct access to source documents is required for these periodical inspections. An audit may be performed at any time by persons authorized by the sponsor and independent of the person in charge of the trial. This audit may be performed at the sponsor site and/or on-site and includes a review of source data. For the same purpose, an inspection may be done at any time, by representatives of the relevant health authorities.

### Current state of progress

The recruitment period was from 27 December 2021 (inclusion of the first participant) to 17 January 2024 (inclusion of the last participant). Follow-up is ongoing and expected to be completed by the end of January 2025, with communication of results by mid-2025.

### Protocol amendments

Since the first approved version of the protocol (version 1.0 of 13 September 2021), several protocol amendments were made. Major changes were related to eligibility criteria (documentation of paroxysmal AF, documentation of LA diameter and LV ejection fraction, contraception, formalization of the indication for PVI/AF ablation), study examination and randomization timeframes to resolve scheduling difficulties, precisions on the investigational procedure and redo procedures, and authorized treatments and procedures. The currently approved version is version 7.0 of 19 June 2023.

## Discussion

The BEAT PAROX-AF trial is a prospective multicentre randomized trial which aims to compare the use of PFA with standardized RF ablation (using the CLOSE protocol) in patients receiving their first-time catheter ablation for symptomatic drug-refractory AF. Over the last decades, catheter ablation to achieve PVI has emerged as the ‘cornerstone’ strategy when treating symptomatic AF.^2–4^ To achieve reliable PVI, several energy sources have been developed, all to deliver durable lesions while also proving high patient safety and an effective procedural workflow. As of today, the most commonly used ablation modalities are RF or cryo-ablation-based, using conductive heating or cooling to destroy the targeted tissue.^26,27^ The FIRE AND ICE trial from 2016 which compared these aforementioned ablation strategies has demonstrated ablation using a cryo-balloon to be non-inferior in regard to efficacy and safety compared with standard RF-based ablation in patients with paroxysmal AF.^5,28^ Single-procedure 1-year success rates of both ablation modalities are estimated to range between 50% and 80%. Patients with persistent AF have notably lower success rates compared with those with paroxysmal AF.^2,4,6^ In elite single-centre reports, the success rate for eliminating symptomatic AF (inclusive of both paroxysmal and persistent AF) varies from 55–77%, with many patients requiring multiple procedures.^24,29,30^ New ablation techniques and devices continue to be developed to improve safety and efficacy while reducing procedure time and complexity. Over recent years, PFA has emerged as a novel non-thermal energy source using electroporation to create durable ablation lesions while also providing cardioselectivity leaving other tissues unharmed.^14,15,31^ In a 2021 multicentric safety and feasibility study which enrolled 121 patients with paroxysmal AF, Reddy *et al.* reported a 1-year freedom from any atrial arrhythmia of 84.5 ± 5.4% when using optimized biphasic energy with a single-shot PFA device. Primary adverse events were low at 2.5% with procedure times averaging 92 min.^15,32^ Furthermore, results of several studies indicate that, unlike thermal-based ablation strategies, PFA does not seem to induce any form of oesophageal or nerve injury.^14,31,33,34^ The ADVENT trial which was published in late 2023 is the first prospective randomized non-inferiority trial to compare PFA with thermal ablation strategies (RF ablation or cryo-balloon ablation) in patients with paroxysmal AF.^35^ In this US-based trial, PFA was non-inferior to thermal-based ablation concerning the composite primary efficacy endpoint of initial procedural failure, documented atrial tachyarrhythmia after a 3-month blanking period, AAD use, cardioversion, or repeat ablation.^35^ Importantly, the operators in this trial had limited experience with PFA and many were still in the learning curve phase with this technology as compared with many years of practice using thermal strategies.^35^ The BEAT PAROX-AF trial aims to demonstrate PFA superiority over RF in a European setting. The operators in this trial have performed a significant number of PFA cases prior to enrolling patients into the study. Furthermore, the predefined sub-studies will further enhance our in-depth understanding of this promising new technology. Overall, PFA has the potential to revolutionize the field of cardiac electrophysiology, promising to provide a safer, more effective, and faster ablation strategy when compared with conventional ablation modalities. Therefore, the BEAT PAROX-AF trial and its sub-studies aim to provide much-needed reliable randomized data regarding PFA and critical insights into the optimal treatment approach for paroxysmal AF.
